#### Relevant concomitant care permitted or prohibited during the trial

During the trial intervention period, participants will be asked to maintain their usual dietary patterns and routine curriculum-based activities. Dietary intake will be recorded using a standardized 3-day 24-hour dietary recall, including 2 weekdays and 1 weekend day (52). Total energy intake derived from the dietary recalls will be summarized by group and used to contextualize outcomes plausibly influenced by dietary intake. Compulsory physical education (PE) classes required by the university curriculum will be permitted and recorded, as these classes represent routine curriculum-based activities rather than additional voluntary structured exercise training. Participants will be asked not to initiate any additional structured exercise training outside compulsory PE classes and the allocated trial intervention during the study period. Recorded compulsory PE exposure will be summarized by group and considered when interpreting the trial findings.

#### Provisions for post-trial care

The interventions in this study pose a low risk of injury, and previous similar studies have rarely reported adverse events. To reinforce participant protection, all participants will be covered by accidental injury insurance to address potential intervention-related injuries during the trial. If someone becomes hurt, they will receive the medical help they need until all of their symptoms go away after the trial ends, and the costs will be covered by insurance. The research team will call participants three months after the trial to check their health and look for any long-term effects of the intervention.

### Outcomes

#### Primary outcome measure

The single primary outcome of this trial is CRF, operationalized as maximal oxygen uptake (VO_2_max).

##### Cardiorespiratory fitness

VO_2_max is the classical marker for evaluating CRF and an independent prognostic factor for cardiovascular disease (53, 54). VO2max will be assessed using a standardized graded exercise test (GXT) (55, 56). Before testing, the Cosmed K4b² Portable Metabolic System (COSMED S.R.L., Rome, Italy) and h/p/cosmos^®^ recommended system configuration (h/p/cosmos sports & medical gmbh, Germany) will be calibrated to ensure treadmill speed and incline accuracy within ±0.2 km/h and ±0.5%, respectively. Test termination criteria will include a respiratory exchange ratio (RER) >1.10, ≥95% of age-predicted maximal heart rate (57), a VO_2_ plateau (<2mL·kg^-^¹·min^-^¹ over 30s) (58), or participant request to stop. The mean VO_2_ over the final 30s will be recorded and interpreted according to ACSM guidelines (59).

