### Eligibility criteria

Inclusion criteria include the following:

Full-time university students aged 18–32 years.Low self-reported physical activity, defined as ≤1.5 h/week of moderate-to-vigorous physical activity (MVPA), and high sedentary exposure, defined as ≥6 h/day of sedentary time, assessed using the International Physical Activity Questionnaire (IPAQ) (44).Completion of a health history questionnaire (45), Physical Activity Readiness Questionnaire (PAR-Q+) (46) and electrocardiogram screening to exclude potential cardiac rhythm abnormalities prior to enrollment.Provision of written informed consent and willingness to comply with the intervention and assessment procedures.

Exclusion criteria include the following:

Self-reported MVPA exceeding the eligibility threshold, or participation in additional structured exercise training outside compulsory physical education classes.Current or recent musculoskeletal, cardiovascular, respiratory, metabolic, neurological, or psychiatric conditions that may contraindicate vigorous stair-climbing exercise or limit safe participation.Use of medications or treatments that may substantially affect cardiovascular, metabolic, inflammatory, or psychological outcomes.Majoring in sports science or exercise-training-related disciplines, to minimize confounding from discipline-specific curricular training, exercise literacy, habitual structured-activity exposure, and potential intervention contamination.Inability to comply with the intervention schedule, assessment procedures, or follow-up requirements.

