Zhou et al. (42)	Sedentary obese adults; stair-climbing exercise snacks	Participants performed stair-climbing exercise snacks 4 days/week for 12 weeks; each snack involved ascending four flights of stairs, 6 times/day, with intervals >1 h	12 weeks	Informed the 12-week duration and VO_2_max-based sample-size assumptions; the specific prescription of 4 days/week, 6 sessions/day, and 60 steps/session was not adopted

This table summarizes prior exercise-snack and related short-bout exercise studies considered during intervention development, including studies differing in design, duration, exercise mode, and population. The final column describes how each study informed the present protocol. FITT, frequency, intensity, time, and type; HRmax, maximum heart rate; HIIT, high-intensity interval training.

The intervention follows a two-phase dose-progression design to accommodate the gradual familiarization of sedentary university students with vigorous short-bout stair climbing.

Basic adaptation phase (Weeks 1–6): Participants will complete three sessions per day on three days per week. Each session will comprise three 30-s vigorous stair-climbing sets, corresponding to 90 s of effective stair-climbing time per session. Sets will be performed as rapidly as safely possible, with a target intensity of 80%–95% of predicted maximum heart rate (HRmax), estimated as 208 − 0.7 × age (47). This phase is intended to familiarize participants with the stair-climbing protocol, support tolerance to vigorous short-bout exercise, and establish regular participation within campus routines.Intensive progression phase (Weeks 7–12): The target intensity, daily session frequency, and weekly frequency will remain unchanged. The number of 30-s stair-climbing sets will increase from three to four per session, corresponding to 120 s of effective stair-climbing time per session. This progression is intended to increase the total stair-climbing dose while preserving the same distributed within-day structure and recovery pattern (48).

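### The graded exercise test lists maximal-effort checks as alternative stopping rules, so the recorded VO2max, the single primary outcome, may be submaximal in many participants

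*Protocol article*

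**What the plan says.** Under Primary outcome measure: "The single primary outcome of this trial is CRF, operationalized as maximal oxygen uptake". The Cardiorespiratory fitness section then describes a graded treadmill test with gas analysis. On how the test ends it says: "Test termination criteria will include a respiratory exchange ratio (RER) >1.10, ≥95% of age-predicted maximal heart rate". The sentence goes on to a VO2 plateau, defined as a change below 2 mL/kg/min over 30 s with no reference to workload, and closes with "or participant request to stop". The value carried forward is defined next: "The mean VO_2_ over the final 30s will be recorded".

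The section does not say that the test continues to exhaustion, or that more than one criterion must be met. No other part of the article changes this reading.

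The Sample size section plans on a VO2max difference of 3.5 mL/kg/min and an SD of 4.44, and arrives at 26 per group before attrition. Statistical methods specifies ANCOVA on post-intervention VO2max, adjusted for baseline.

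**The concern.** RER above 1.10, a heart rate near the predicted maximum and a plateau are evidence that a participant has reached a maximum. Used as rules that end the test, they can prevent the participant from reaching it:

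- **Heart rate.** A stop at 95% of a predicted maximum makes the recorded VO2 depend on how far the individual's true maximum lies from the prediction.
- **RER.** Passing 1.10 supports maximal effort but does not show that VO2 has stopped rising.
- **Plateau.** Because it is not tied to a rise in workload, a steady state within a stage, or an ordinary rise on a slow ramp, can satisfy it.

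The measurement at issue is the only confirmatory endpoint. If many tests end early, the estimate mixes change in maximal capacity with error in heart-rate prediction. It could also pick up any change in heart rate or RER at a given workload. A submaximal recording cannot be repaired at the analysis stage.

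**Working it through.** **1. The plan's own figure.** Pooled SD = √[(3.87² + 4.95²)/2] = 4.44, and d = 3.5/4.44 = 0.79. The normal-approximation formula gives 26 per group, and 26/0.9 rounds up to 29. With the exact t distribution, power for d = 0.79 is 79.8% at 26 and 81.3% at 27 per group. The stated sample size reproduces.

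**2. Inputs for the shortfall.**
- From the documents: the 95% threshold; ages ("Full-time university students aged 18–32 years"); VO2max levels of 32.06 and 37.61 mL/kg/min from the source trial; SD 4.44; target difference 3.5.
- Assumed: percentage of heart-rate reserve equals percentage of VO2 reserve; resting VO2 3.5; resting heart rate 70.
- Also assumed: the prediction "estimated as 208 − 0.7 × age" applies to the test. The article gives this formula for training intensity and states none for the test.

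**3. Shortfall at a heart-rate stop, age 20.** Predicted maximum = 208 − 0.7 × 20 = 194, and the stop is at 0.95 × 194 = 184.3 bpm. (The stop is 185.6 bpm at age 18 and 176.3 at age 32.)

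Shortfall = [1 − (184.3 − 70)/(true HRmax − 70)] × (VO2max − 3.5), and 0 if true HRmax is below the stop.

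| True HRmax vs prediction | Fraction of reserve at stop | VO2max 32.06 | VO2max 37.61 |
|---|---|---|---|
| −10 bpm | 1 | 0 | 0 |
| 0 | 114.3/124 = 0.922 | 2.2 | 2.7 |
| +5 bpm | 114.3/129 = 0.886 | 3.3 | 3.9 |
| +10 bpm | 114.3/134 = 0.853 | 4.2 | 5.0 |

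A shortfall above 3.5 needs a true maximum about 6 bpm (VO2max 32.06) or 3 bpm (37.61) above prediction.

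**4. Sensitivity to the prediction formula.** If the predicted maximum were 200, the stop would be at 190. With true HRmax 194, resting heart rate 70 and VO2max 35, the shortfall is (1 − 120/124) × 31.5 = 1.0.

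**5. Effect on the comparison.** If the stop fraction is the same in both arms, a true difference of 3.5 is recorded as about 3.5 × 0.922 = 3.2. A simulation used mean VO2max 32.06, SD 4.44, age 20, the heart-rate rule alone, and an assumed SD of true HRmax around prediction:

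| SD of HRmax (bpm) | Stopped before maximum | Mean shortfall | Shortfall above 3.5 | Recorded difference | Recorded SD | Power, 26 per group |
|---|---|---|---|---|---|---|
| 5 | 97% | 2.2 | 12% | 3.23 | 4.23 | 77% |
| 7 | 92% | 2.2 | 19% | 3.23 | 4.31 | 75% |
| 10 | 83% | 2.3 | 26% | 3.22 | 4.45 | 73% |
| 12 | 79% | 2.4 | 29% | 3.21 | 4.53 | 71% |

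The power figures are for the unadjusted comparison that the sample size uses. Baseline adjustment would absorb part of any prediction error that repeats at both visits; this was not calculated.

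**6. A part that would not cancel.** Under the same assumptions with true HRmax 194, VO2 rises by 28.56/124 = 0.23 to 34.11/124 = 0.28 mL/kg/min per bpm. Suppose, for illustration, that training lowers heart rate at a given workload by 5 bpm. A test ended by the heart-rate rule would then stop 1.2-1.4 mL/kg/min higher in the exercise arm with no change in VO2max. That is 33-39% of the target difference. The document gives no figure for such a shift.

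**7. The other criteria.** An RER stop at an assumed 95%, 90% or 85% of VO2max falls short by 1.6-1.9, 3.2-3.8 or 4.8-5.6 mL/kg/min. For the plateau, a ramp of r mL/kg/min per minute raises VO2 by r/2 in 30 s, so any ramp below 4 meets the criterion without a true plateau. The article gives no ramp rate.

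**The case against.** The strongest reply is that this is loose wording in a condensed article. The cited testing standards, not shown here, may set the stage structure and how criteria are counted. That weakens any estimate of how often tests would end early, but it does not remove the problem. The list is headed as termination criteria, is joined by *or*, and includes participant request, which makes sense only as a reason to stop. The article has fixed the rule and nothing else in it corrects the rule.

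Several further objections stand and limit the point:

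- A reader might infer that the recorded value is not VO2max at all. The document does not support that. Tests that end at a true plateau or at exhaustion are maximal, and so are tests in people whose maximum lies at or below the heart-rate threshold.
- A reader might infer that the error exceeds the 3.5 target difference. That compares one person's shortfall in level with a difference between groups. The same test is used in both arms at both visits by blinded technicians, so a common shortfall largely cancels. Even for individuals, more than 3.5 is a minority result (12-29% under the assumed spread).
- The differential bias in step 6 is a possibility. The document neither states nor quantifies a training shift in heart rate or RER.
- The planning SD cannot be called mismatched, because the article does not say how the source trial ended its tests.
- Participant request is not itself a defect. A test to exhaustion also ends when the participant stops, and that right must remain.

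**Conclusion.** The point holds as a defect in the stated definition of the primary measurement. Followed literally, the rule can end tests before maximum and record the result as VO2max.

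Under the assumed physiology the typical individual shortfall is about 2-3 mL/kg/min, ranging from 0 to about 5 for true maxima 10 bpm either side of prediction. For the treatment comparison, the common part gives modest attenuation (3.5 recorded as about 3.2) and added variation between people, with power about 71-77% instead of about 80% at 26 per group. With 27 per group, which is 30 less 10% attrition, the corresponding power is 72-79% instead of 81%. A training shift in heart rate or RER would add a bias between arms of unknown size. Baseline-adjusted ANCOVA cannot remove it, because it arises after randomisation.

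All of these sizes rest on the heart-rate reserve relation, the borrowed prediction formula, the resting values and the assumed spread. None is a fact in the document. That the rule can end a test early follows from the text alone and needs no such assumption.

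**What to change.** Reword the Cardiorespiratory fitness section before testing begins:

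- Make RER, heart rate and plateau criteria for verifying maximal effort after the test, not rules that end it.
- Define the plateau as a rise in VO2 below the threshold despite an increase in workload.
- State how many criteria must be met, and which heart-rate prediction formula applies to the test.
- Leave the investigators' safety stops and the participant's right to stop unchanged.
- Report attainment by arm and visit.

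Keep every test in the primary intention-to-treat analysis, whether or not it met the criteria. An analysis restricted to tests that met them can be supportive only, because it conditions on something observed after randomisation.

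The cost is a change of wording and somewhat longer tests. The article gives no ramp rate from which to say how much longer.

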#### Secondary outcome measures

Secondary outcomes will include mental health indicators, body anthropometry, body composition, blood pressure, and vital capacity. These outcomes will provide supportive evidence regarding the broader physical and psychological effects of the intervention.

##### Body anthropometry

Body mass index (BMI) is a classical marker of overall obesity and is positively associated with cardiovascular risk (60). Participants will fast for at least 4hours before measurement. Height and weight will be assessed with an ultrasonic height and weight scale (DHM-30, Zhengzhou Dingheng Electronic Technology Co., Ltd.), and BMI will be calculated as weight/height² (61). Waist circumference will be measured with a soft tape (Deli Group, Ningbo, China) at the midpoint between the lowest rib and iliac crest, with a precision of 0.1 cm, at the end of normal expiration. Hip circumference will be measured at the level of maximum gluteal protrusion (62). Both waist and hip circumferences will be measured three times, and the mean will be recorded.

##### Body composition

Body fat percentage is an independent predictor of metabolic syndrome and is positively associated with insulin resistance (63, 64). Body composition—including basal metabolic rate (BMR), body fat percentage (FAT%), fat-free mass (FFM), total body water (TBW), extracellular water (ECW), and intracellular water (ICW)—will be assessed using the Bodystat^©^ QuadScan 4000 (Bodystat Ltd, UK). Participants will rest for 15minutes before testing and avoid vigorous exercise, alcohol, food, and water intake for at least 2 hours. Measurements will be conducted supine with electrodes attached to standard sites, and participants will remain relaxed.

##### Blood pressure

Abnormal blood pressure in young adults damages endothelial function and serves as an early warning of cardiovascular risk (65). Participants will be advised to sleep adequately and avoid vigorous activity, caffeine, and alcohol before testing. Blood pressure will be measured using an electronic sphygmomanometer (Yuwell YE600F, Jiangsu Yuwell Medical Equipment Co., Ltd.). The cuff will be placed on the left upper arm at heart level. Three measurements will be taken at 1-minute intervals, with the mean systolic (SBP) and diastolic (DBP) pressures used for analysis.

##### Vital capacity

Reduced vital capacity compromises cardiopulmonary reserve and oxygen delivery, increasing cardiovascular disease risk; it is a key indicator linking respiratory and cardiovascular health (66, 67). Vital capacity will be assessed using an electronic spirometer (FCS-10000, Shanghai Yilian Medical Instrument Development Co., Ltd.). The mouthpiece will be disinfected before testing. Participants will stand upright, hold the handle, inhale maximally to total lung capacity, then exhale smoothly to residual volume. The test will be repeated twice, and the highest value (ml) will be recorded.

##### Mental health

Psychological outcomes will be assessed using validated Chinese-language instruments selected to capture prespecified psychological and psychosocial domains relevant to sedentary university students, including depressive symptoms, perceived stress, mood state, general well-being, sleep quality, perceived social support, resilience, and body appreciation. These outcomes will be interpreted according to a prespecified hierarchical framework rather than as a single composite construct, because the selected instruments assess distinct but related psychological and psychosocial dimensions.

Depressive symptoms and perceived stress will be treated as key secondary psychological outcomes and assessed using the Beck Depression Inventory-II (BDI-II) (68) and 10-item Perceived Stress Scale (PSS-10) (69), respectively. Mood state, general well-being, and sleep quality will be treated as supportive psychological outcomes and assessed using the Profile of Mood States (POMS) (70), General Well-Being Schedule (GWBS) (71), and Pittsburgh Sleep Quality Index (PSQI) (72). Perceived social support, resilience, and body appreciation will be treated as exploratory psychosocial indicators and assessed using the Multidimensional Scale of Perceived Social Support (MSPSS) (73), Resilience Scale (74), and Body Appreciation Scale-2 (BAS-2) (75). Baseline covariates will include demographic characteristics and health behaviors, including smoking, alcohol use, and sedentary time.

#### Exploratory outcome measures

Exploratory mechanistic outcomes will include glycolipid metabolism, inflammatory markers, and adipokines. These outcomes will be used to explore potential metabolic, inflammatory, and adipokine-related pathways through which stair-climbing ES may influence health.

All biological sample collection and analyses will be performed in line with standardized protocols. Specifically, a 10-hour fasting period for participants, venous blood sampling from the antecubital vein between 7:00 and 9:00 AM, and aliquoting into EDTA anticoagulant tubes or clot activator tubes based on assay specifications. To ensure sample quality, low-temperature centrifugation will be completed within 30 minutes post-collection. Serum and plasma will be separated, stored at -80 °C in ultra-low temperature freezers, and protected from repeated freeze-thaw cycles until batch analysis (76).

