#### Intervention description

The ES group will receive a 12-week structured stair-climbing ES intervention (**Figure 3**; **Table 1**). The prescription was developed with reference to prior ES and related short-bout exercise studies summarized in **Table 2**, while the final FITT structure was aligned primarily with Yin et al. (41). Specifically, Yin et al. informed the adopted weekly frequency, within-day distribution, 30-s stair-climbing unit, between-session spacing, stair-climbing mode, and vigorous intensity-monitoring framework. The 12-week intervention duration was selected with reference to longer-duration ES evidence, including Zhou et al. (42). Overall, the adopted prescription was selected to balance feasibility, safety, and a sufficient vigorous stair-climbing stimulus in sedentary university students. In the present protocol, ES is operationalized as a distributed short-bout stair-climbing intervention within the broader framework of short bouts of accumulated exercise. The unit of within-day distribution is the short stair-climbing session: participants complete three sessions on each intervention day, separated by 1–4 h. Within each session, three to four 30-s vigorous stair-climbing sets separated by active recovery constitute the prescribed stair-climbing dose. Thus, the protocol preserves the distributed within-day structure of ES while transparently specifying the clustered set structure used to deliver a standardized stair-climbing stimulus.

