### Participant timeline

This study will include two main assessment time points: baseline and post-intervention. The primary outcome, secondary outcomes, exploratory outcomes, and descriptive data will be collected at these time points. Each assessment phase will be completed within one week to minimize temporal variation in outcome measurement. For participants in the ES group, post-intervention VO_2_max assessment will be scheduled 48–72 h after the final completed intervention session, including any make-up session, and this interval will be recorded.

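### The 48–72 h gap after the last training session is set and recorded for VO2max only, so an acute last-session effect in the ES arm could mix into the other 12-week contrasts

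*Protocol article*

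**What the plan says.** All of this is in the protocol article.

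- **VO2max (Participant timeline).** The rule covers ES participants and reads: "post-intervention VO_2_max assessment will be scheduled 48–72 h after the final completed intervention session, including any make-up session, and this interval will be recorded".
- **All other outcomes (Participant timeline).** The general rule is "Each assessment phase will be completed within one week to minimize temporal variation in outcome measurement". No minimum time since training is attached to it.
- **Bloods (Exploratory outcome measures).** The conditions are "a 10-hour fasting period for participants, venous blood sampling from the antecubital vein between 7:00 and 9:00 AM", plus sample handling. There is no exercise-free interval.
- **Blood pressure.** "Participants will be advised to sleep adequately and avoid vigorous activity, caffeine, and alcohol before testing". No number of hours is given.
- **Body composition.** Participants are to "avoid vigorous exercise, alcohol, food, and water intake for at least 2 hours".
- **Psychological scales (Mental health).** The section ranks the instruments, for example "Mood state, general well-being, and sleep quality will be treated as supportive psychological outcomes", but sets no timing relative to exercise.
- **Exposure (Intervention description, Table 1).** In the ES arm, "participants complete three sessions on each intervention day, separated by 1–4 h", on three days a week at 80–95% of predicted maximal heart rate. Controls keep their usual lifestyle and have no trial sessions (Study design).
- **Analysis (Statistical methods).** Secondary and exploratory outcomes use baseline-adjusted models like the primary ANCOVA. The model described there has no term for time since the last session.

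**The concern.** The VO2max rule shows that the authors regard recent training as something to keep out of the post-intervention measurement. The same care is not extended to glucose, insulin, HOMA-IR, lipids, cytokines, adipokines, blood pressure, body composition or mood, some of which may also respond in the short term to vigorous exercise.

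The exposure depends on allocation. Controls have no last session, so a carry-over would not be noise shared by both arms; it would shift one arm. Blinded assessment and randomisation do not prevent this, because it arises after randomisation and is present in the measurement itself.

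At stake is what the secondary and exploratory estimates mean. They are offered as effects of a 12-week programme and as clues to its mechanisms. A reading taken the morning after a training day could partly reflect that day. The shift could flatter the intervention or count against it, depending on the outcome. Since the interval is to be recorded for VO2max only, the problem might not be checkable afterwards.

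**Working it through.** **1. Time since training that each stated condition allows**

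| Outcome | Stated condition | Shortest gap compatible with the text |
|---|---|---|
| VO2max | 48–72 h after last session, recorded | 48 h |
| Bloods | 10 h fast, draw at 07:00–09:00 | in practice overnight to about a day |
| Blood pressure | avoid vigorous activity, no duration | undefined |
| Body composition | at least 2 h without vigorous exercise | 2 h |
| Questionnaires | none | same day |

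The article gives no clock times for sessions. Assume that the last session of the day ends between 12:00 and 22:00 and blood is drawn the next morning:

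- End at 12:00, draw at 09:00: 12 + 9 = 21 h.
- End at 22:00, draw at 07:00: 2 + 7 = 9 h.

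The gap is then 9–21 h, well under 48 h.

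**2. Why baseline adjustment does not help**

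ANCOVA estimates the difference in post-intervention means given baseline. Write the ES post-intervention mean as control mean + training effect + acute shift. Baseline is measured before any trial session and carries no information on the acute shift. The adjusted difference therefore estimates training effect + acute shift, and the two cannot be separated.

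**3. How large the consequence could be (illustration)**

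Inputs:
- Analysed per arm: 27, from the planned 30 less 10% attrition (Sample size): 30 × 0.9 = 27.
- Two-sided 5% level, as in the plan.
- Assumed, not in the documents: baseline correlation r = 0.5–0.7; mean acute shift s = 0.1–0.5 SD in the ES arm; true training effect zero.

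Formulas:
- Residual df = 54 − 3 = 51; t(0.975; 51) = 2.008.
- CI half-width = 2.008 × √(1 − r²) × √(2/27).
- Noncentrality = [s / √(1 − r²)] × √(27/2). The probability that the CI excludes zero comes from the noncentral t.

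Half-width:
- r = 0.5: 2.008 × 0.866 × 0.272 = 0.47 SD.
- r = 0.7: 2.008 × 0.714 × 0.272 = 0.39 SD.

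Probability that the 95% CI excludes zero, per outcome:

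| Mean shift s | r = 0.5 | r = 0.7 |
|---|---|---|
| 0.10 SD | 7.0% | 8.0% |
| 0.20 SD | 13.2% | 17.3% |
| 0.25 SD | 18.0% | 24.3% |
| 0.30 SD | 23.9% | 32.8% |
| 0.50 SD | 54.8% | 71.4% |

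The nominal value is 5%.

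**4. Dilution**

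The shift in the table is an average over the ES arm. If an individual carry-over of 0.2–0.5 SD is present in only half of the ES participants, the mean shift is 0.5 × 0.2 = 0.10 to 0.5 × 0.5 = 0.25 SD. The probabilities then fall to 7–8% and 18–24%. The 55–71% row needs every ES participant to be measured while a full 0.5 SD carry-over is present.

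**The case against.** The strongest reply is that a missing rule is not a schedule. The article permits early measurement but does not plan it. The figure with the assessment timeline is not shown here, and visit order is something an article may leave to the full protocol. If all measures were taken at the VO2max visit before the treadmill test, the problem would not arise. This stands: a reader might infer that an acute effect will be reported as a 12-week effect, and the text supports only that it could be. The reply does not dispose of the point, because the article does state preparation conditions outcome by outcome and limits the interval rule to one of them.

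Further objections, and what remains of them:

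- **A gap of a few hours is unrealistic for bloods.** Correct. A fasting draw at 07:00–09:00 makes overnight the practical minimum. Same-day measurement is open mainly for body composition and questionnaires. Blood pressure has partial protection.
- **The size is assumed.** Correct. No passage says how far any outcome moves after these sessions, and the daily dose is small: 360 s of stair climbing in Weeks 7–12 (Table 1). Scales asking about a longer past period would also be less exposed than momentary mood.
- **The outcomes are not confirmatory.** Correct. Statistical methods treats them as supporting or hypothesis-raising and puts the weight on estimates and intervals. However, a carry-over would move exactly those estimates.
- **Compulsory physical education exposes both arms.** True, but it is not assigned by randomisation. Only trial sessions differ by arm by design.

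**Conclusion.** The concern holds in limited form. The stated conditions leave the non-VO2max outcomes open to measurement sooner than 48 h after a training day that only the ES arm has, and the planned model cannot separate a last-session response from a training effect. The primary VO2max comparison is not affected.

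The size is unknown. Under an assumed mean shift of 0.1–0.5 SD, with 27 per arm and r = 0.5–0.7, the CI for an affected outcome would exclude zero in about 7–71% of trials with no training effect. This range shows sensitivity and does not estimate bias in this trial; its upper end is a worst case. Nor do the documents show that these outcomes will in fact be measured early.

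This is a cheap improvement worth making before post-testing starts, because no later analysis could reliably correct the problem.

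**What to change.** In Participant timeline, extend the rule: for the ES group, every post-intervention outcome sensitive to recent exercise (bloods, blood pressure, body composition, mood and the other scales) is measured at least 48 h after the last completed trial session, including any make-up session, and within the existing one-week phase. Record the interval for each of these, as is already planned for VO2max. Any of them measured on the VO2max day should be taken before the treadmill test. The preparation notes for blood pressure and body composition should then point to this rule.

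Doing everything on one morning is optional. Study setting lists the blood laboratory separately from the exercise and psychology laboratories, so it should not be assumed that one visit would suffice.

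The cost is a sentence or two in the protocol, one extra recorded field and tighter booking of the ES assessment week. The intervention, sample size and analysis model stay as they are.
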